Time points (week)	0	1	2	3–4	5	6–9	10	11–14	15	16–20	21	43
Outcomes (evaluator rating)												
GRID-Hamilton Rating Scale for Depression	IE						IE				IE	IE
Structural Interview Guide for Hamilton Anxiety Rating Scale	IE						IE				IE	IE
Clinical Global Impression	IE						IE				IE	IE
General Assessment of Functioning	IE						IE				IE	IE
Structural clinical interview for DSM	IE										IE	IE
Outcomes (self-report)												
Overall Anxiety Severity and Impairment Scale	P	P	P	P	P	P	P	P	P	P	P	P
Overall Depression Severity and Impairment Scale	P	P	P	P	P	P	P	P	P	P	P	P
Disorder Specific Measures	P						P				P	P
EQ-5D	P						P				P	P
Sheehan Disability Scale	P						P				P	P
Sense of Authenticity Scale	P						P				P	P
Treatment mechanism												
Eysenck Personality Questionnaire Revised-Short version, Neuroticism subscale	P				P		P		P		P	P
Anxiety Sensitivity Inventory-III	P				P		P		P		P	P
Emotion Regulation Skills Questionnaire	P				P		P		P		P	P
Emotion Exposure Questionnaire	P				P		P		P		P	P
Treatment Rationale for Unified Protocol	P				P		P		P		P	P
Process measures												
Session Rating Scale		P/T			P/T		P/T		P/T			
Credibility/Expectancy Questionnaire			P/T									
Homework Compliance Scale			T	T	T	T	T	T	T	T		
Adverse Event			T	T	T	T	T/IE	T	T	T	IE	IE
Neurological correlates												
Functional Magnetic Resonance Imaging	X										X	X

*IE* assessment of independent evaluator, *P* patient self-report, *T* therapist self-report

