### Discontinuation

Any participant in the intervention group who meets any of the discontinuation criteria will have their intervention (UP) stopped. Where possible, subsequent assessment will be conducted.Participant request for discontinuation or participant withdrawal of consent.Inability to contact the participant for a month.Difficulty continuing the intervention because of a severe adverse event.Difficulty continuing the intervention because of the exacerbation of comorbid symptoms.Participant proves after assignment not to fulfill the eligibility criteria.The whole clinical trial is stopped.Any other reason that the primary investigator, therapist, and supervisor agree to warrants discontinuation.

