### Statistical methods

All analyses for testing efficacy of treatment on primary and secondary measures will be analyzed on the basis of the intent-to-treat principle, using a linear mixed model (LMM). The LMM approach was selected because of its strength in dealing with missing data and its ability to incorporate random effects (i.e., of the participants) into the analyses. For the primary outcome, the dependent variable is the GRID-HAMD score, and the independent variables are assignment (i.e., intervention vs. control group), time (i.e., 0, 10, and 21 weeks), and interaction of the assignment and time, as a fixed-effect variable, and participants, as random-effects variable. We will construct a conditional growth model [121] using a restricted maximum likelihood estimation method to compare changes in depression severity between groups from baseline to 21 weeks. The assessment period is measurement time for the growth model (weeks 0, 10, and 21), which will be coded as an ordinal scale (0, 1, 2). We assume an unstructured error covariance for this model. If the analysis will not converge, we will use other covariance structures. The covariance structure that will show convergence of the analysis and best fit to the data, evaluated by Akaike’s information criterion, will be used as the primary analysis.

To test robustness, we will conduct the same LMM, including a stratified variable (depressive vs. anxiety disorder) as covariate and other sensitive analyses taking into account the following aspects: ITT vs. per-protocol, and multiple imputation methods for missing data [122]. Secondary outcomes will be analyzed in the same way as primary outcomes. For all analyses, *P* < .05 will be considered statistically significant. The other statistical analyses will be conducted to examine treatment mechanism, process, and neurological implications in relation to outcome.

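### The one missing-data robustness check the article names is unspecified multiple imputation, which in its usual form shares the primary mixed model's missing-at-random assumption and does not test it

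*Protocol article*

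**What the plan says.** Statistical methods makes a linear mixed model fitted by restricted maximum likelihood the primary analysis, with group, time and their interaction as fixed effects. On missing data it says "The LMM approach was selected because of its strength in dealing with missing data". The GRID-HAMD enters at three time points only: "The assessment period is measurement time for the growth model (weeks 0, 10, and 21".

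The robustness analyses follow in one sentence. It begins "To test robustness, we will conduct the same LMM, including a stratified variable (depressive vs. anxiety disorder) as covariate" and then lists "ITT vs. per-protocol, and multiple imputation methods for missing data", with a citation. It does not give the type of imputation, the variables used or the missing-data assumption, and it names no analysis that departs from missing at random.

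The Discontinuation section covers the treated arm: "Any participant in the intervention group who meets any of the discontinuation criteria will have their intervention (UP) stopped". One of its seven reasons is "Difficulty continuing the intervention because of the exacerbation of comorbid symptoms"; others are a severe adverse event and a month without contact. It adds: "Where possible, subsequent assessment will be conducted".

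Table 2 schedules the self-report "Overall Depression Severity and Impairment Scale" (ODSIS) and its anxiety counterpart (OASIS) at every listed time point from week 0 to week 21, and again at week 43.

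**The concern.** A likelihood-based mixed model gives valid estimates when data are missing at random, that is, when missingness depends only on what has been observed. Ordinary multiple imputation makes the same kind of assumption. If the imputation model contains only the variables already in the mixed model, the two are close to being one analysis done twice. Their agreement could be reported as robustness although the assumption at risk was never relaxed. The other two checks named do not fill the gap: adding the stratification factor does not address unobserved reasons for loss, and the per-protocol comparison is not a missing-data method.

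This matters because loss linked to worsening is foreseeable. The GRID-HAMD is not rated between weeks 10 and 21. A patient who deteriorates in that interval and is then lost leaves no trace of it in the scores the primary model uses. At stake is the credibility of a robustness claim in a small trial, where about four patients per arm (0.15 × 27 = 4.05) are expected to drop out.

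**Working it through.** **Inputs from the article (Sample size calculation, Statistical methods).** Effect size 0.85; power 80%, two-tailed; significance level 0.05; 23 per group, raised to 27 for 15% dropout; dropout in earlier studies 11.76% to 15.39%.

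**The plan's own figure.** A two-sample noncentral t calculation at d = 0.85 gives power 0.786 with 22 per group and 0.805 with 23, so 23 is reproduced. For dropout, 23/0.85 = 27.06, against the stated 27. Neither figure bears on the missing-data assumption; they only fix the scale for what follows.

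**Step 1. Size of a departure from missing at random.** Suppose a fraction m of UP patients has no week-21 rating, these patients are in truth k SD worse than the model predicts, and the control arm is unaffected. Then bias = m × k, and the effect becomes 0.85 − m × k.

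| m | k (SD) | Bias (SD) | Effect |
|---|---|---|---|
| 15% | 0.5 | 0.075 | 0.775 |
| 15% | 1.0 | 0.150 | 0.700 |
| 15% | 1.5 | 0.225 | 0.625 |
| 15% | 2.0 | 0.300 | 0.550 |
| 11.76% | 1.0 | 0.118 | 0.732 |
| 15.39% | 1.0 | 0.154 | 0.696 |

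The article gives no value for k, so this is a range and not an estimate. The scenario in which unassessed UP patients have the control mean is k = 0.85: bias = 0.15 × 0.85 = 0.1275, effect = 0.85 − 0.1275 = 0.7225, or about 0.72.

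**Step 2. When does imputation differ from the mixed model?** A large-sample simulation of one arm (400,000 patients, true week-21 mean 0, SD 1, 15% missing at week 21, logistic dropout slope 1.5 per SD) used assumed correlations. Baseline correlated 0.5 with week 10 and 0.4 with week 21; week 10 correlated 0.6 with week 21. A late self-report score correlated 0.4, 0.6 and 0.8 with those three scores. A negative value means the arm looks better than it is.

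| What drives dropout | Mixed model, or imputation on the same scores | Imputation with the self-report score added |
|---|---|---|
| Week-10 GRID-HAMD (observed) | 0.00 | 0.00 |
| Late worsening seen on self-report | −0.08 | 0.00 |
| The unseen week-21 score | −0.117 | −0.067 |

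Same-score imputation adds nothing to the mixed model in any row. Imputation with self-report scores exposes the bias fully in the second row and partly in the third. Only an analysis that shifts the imputed values can show what remains.

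**Step 3. Direction.** The simulation applies to whichever arm loses the patients. If it is the UP arm, UP looks better than it is. If deteriorating waiting-list patients leave unassessed, the control arm looks better and the effect is understated. The sample-size section allows for 15% dropout in each group and gives no reason to expect it in one arm only.

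**The case against.** The strongest reply is that the article condenses a fuller plan. The phrase on multiple imputation can cover delta-adjusted or reference-based methods, the cited source is not at hand, and imputation settings usually belong in an analysis plan. That stands as far as it goes: a reader might infer that standard imputation on the same variables is planned, but the text says neither. What remains is that the article itself chooses these analyses and calls them tests of robustness, and none is identified as relaxing the primary model's assumption.

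Three further replies also hold, and they limit the point:

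- A reader might infer that imputation could never reveal the bias. That is too strong. The mixed model conditions on each patient's own scores, so worsening seen at week 10 is already handled, and the frequent ODSIS and OASIS scores could make imputation differ from it.
- A reader might equate stopping UP with a missing outcome. The Discontinuation section separates the two, because assessment is to continue as far as feasible. Only two of the seven reasons (severe adverse event, exacerbation of comorbid symptoms) describe worsening, and the latter is not specific to the GRID-HAMD.
- A reader might conclude that the bias must favour UP, or that 0.72 measures it. The documents support neither. The figure assumes that every UP dropout goes unassessed and has no benefit, and that no control is lost for outcome-related reasons.

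The per-protocol comparison is no separate fault, since it is listed only as a sensitivity analysis beside the intent-to-treat primary.

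**Conclusion.** The point holds in conditional form. If the imputation is of the usual kind and uses the GRID-HAMD scores, it repeats the primary model's missing-at-random assumption and cannot support a claim that the result is robust to it. The primary analysis itself is not in question.

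The size cannot be fixed from the article. At the planned 15% dropout, each SD by which unassessed UP patients are worse than predicted takes 0.15 SD off the effect; the no-benefit scenario takes 0.85 to about 0.72. Both assume that the loss is confined to the UP arm; such loss among controls would act in the opposite direction. The simulated biases of 0.08 to 0.117 SD rest on assumed correlations and an assumed dropout slope. This is a worthwhile, inexpensive improvement to the sensitivity analyses and not a threat to the design.

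**What to change.** Keep the mixed model as primary and make three changes to the missing-data sensitivity analysis:

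1. State the assumption and the variables of the multiple imputation, and include the repeated ODSIS and OASIS scores as auxiliary variables.
2. Prespecify one delta-adjusted tipping-point analysis of week-21 GRID-HAMD. Impute, worsen the imputed UP scores in one-point steps, and report the estimate and p-value at each step until p exceeds 0.05. Readers can then judge whether the tipping shift is plausible.
3. Optionally show a reference-based imputation (missing UP scores drawn from the waiting-list arm) alongside, labelled as a conservative scenario.

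Report the number of patients without a week-21 rating by arm and reason, so that the likely direction of any bias can be seen.

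The cost is extra programming on data already collected, with no added visits or assessments, and possibly a less favourable sensitivity estimate. The article reports 44 participants enrolled towards a target of 54, so the change could still be prespecified at that stage, provided outcomes had not been examined by arm.

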#### Secondary outcomes

Secondary outcomes for treatment efficacy are severity of anxiety assessed by SIGH-A, overall severity and improvement rated by Clinical Global Impression, responder status defined by 50 % or more baseline reduction in score on GRID-HAMD, remission of symptom defined as less than 8 on GRID-HAMD [77], and absence of met psychiatric diagnoses as assessed by SCID-IV-TR at baseline. These secondary measures are assessed at post-treatment (21 weeks).

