#### Clinical Global Impression (CGI)

CGI is an overall clinician rating of the severity of psychopathology (CGI-Severity; CGI-S) and improvement of it (CGI-Improvement, CGI-I) [80]. These are rated from 0 to 7 based on the assessor’s overall evaluation, which incorporates all available information about a patient’s history, psychosocial circumstances, symptoms, behavior, and the impact of symptoms on the patient’s ability to function [81]. In this study, essentially, the independent evaluator assesses the same patient at baseline, mid, post, and follow-up (0, 10, 21, and 43 weeks). Hence, the evaluator’s overall impression of longitudinal change will be reflected in the CGI-I rating.

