#### Structural clinical interview for DSM-IV-TR axis I disorders (SCID-IV-TR)

SCID-IV-TR is a semi-structured interview used to asses the diagnostic status of DSM-IV-TR Axis I disorders [83]. We will administer modules A (Mood Episodes), B (Psychotic Symptoms), D (Mood Disorders), E (Substance Use Disorders), and F (Anxiety Disorders) at baseline to evaluate patients according to the inclusion and exclusion criteria. At post-intervention and follow-up, the independent evaluator administers part of each module to examine the presence or absence of the diagnoses met at baseline assessment. The Japanese version of *SCID-IV-TR* has been utilized in many clinical trials since its publication.

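### Three yes/no secondary outcomes are assigned the primary linear mixed model although they are constant at week 0; a week-21 analysis for binary data should be named

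*Protocol article*

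**What the plan says.** The Statistical methods section assigns one model to all efficacy outcomes. It opens with "All analyses for testing efficacy of treatment on primary and secondary measures will be analyzed on the basis of the intent-to-treat principle, using a linear"; the sentence ends by naming the mixed model. Later it adds "Secondary outcomes will be analyzed in the same way as primary outcomes". For the primary outcome the model is set out in full:

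- The fixed effects are arm, time and their interaction, with a random participant effect and REML estimation.
- Weeks 0, 10 and 21 are coded 0, 1 and 2. Baseline is therefore one of the responses, not a covariate.
- The purpose is "to compare changes in depression severity between groups from baseline to 21 weeks".
- On covariance: "We assume an unstructured error covariance for this model". If the fit does not converge, other structures are tried, and the converging one with the best AIC becomes the primary analysis.

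The Secondary outcomes section lists SIGH-A, CGI severity, CGI improvement, responder status (a fall of at least 50 % in GRID-HAMD from baseline), "remission of symptom defined as less than 8 on GRID-HAMD", and absence of the diagnoses met at baseline. It then says that these measures are assessed at week 21. On the diagnostic interview, the SCID section says "At post-intervention and follow-up, the independent evaluator administers part of each module", and Table 2 shows no SCID at week 10. On CGI improvement, the CGI section says that "the evaluator’s overall impression of longitudinal change will be reflected in the CGI-I rating". The inclusion criteria require a listed diagnosis and a GRID-HAMD score of 8 or more.

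**The concern.** A model that takes the week-0 value as a response needs that value to exist and to vary between patients. It also treats the outcome as continuous with normal errors. Responder status, remission and absence of diagnosis meet neither condition at week 0, and diagnosis has no middle visit either.

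At stake is pre-specification of three secondary results that readers will look for. The rule as written gives a degenerate fit. What is finally reported would then depend on how the software handles a singular matrix, or on a covariance structure picked from the data. The article also gives two pictures of the same outcomes: a single time point in one section and a three-visit growth model in another.

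**Working it through.** The plan gives no figure on this point, so the check sets the sections side by side and then tests the consequence. The sample size is not in dispute: 23 per arm reproduces (two-sample t-test, effect size 0.85, two-sided 0.05, power 0.805). It is used below only to size the simulations.

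**1. Each listed outcome against the stated model** (CGI severity and improvement counted separately, giving six):

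| Outcome | Type | Week 0 | Week 10 | Fits as stated? |
|---|---|---|---|---|
| SIGH-A | score | varies | assessed | yes |
| CGI severity | rating | varies | assessed | yes |
| CGI improvement | rating of change | no value | assessed | only without a week-0 row |
| Responder | yes/no | 0 for all: change from baseline is nil | derivable | no |
| Remission | yes/no | 0 for all: entry at 8 or more, remission below 8 | derivable | no |
| Absence of baseline diagnosis | yes/no | 0 for all: a diagnosis is required for entry | not assessed | no |

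**2. Unstructured covariance.** A three-visit unstructured matrix has 3 × 4 / 2 = 6 parameters. For responder and remission, the three that involve week 0 (one variance, two covariances) are all zero. For diagnosis, the three that involve week 10 have no data, and the week-0 variance and the week 0–21 covariance are zero. Only the week-21 variance is left.

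In one simulated trial of 27 per arm with entry at 8 or more, the determinant of the 3 × 3 sample covariance was 0 for responder and 0 for remission, against about 8011 for the GRID-HAMD score.

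**3. Likelihood.** With N = 54 and residuals of exactly 0 at week 0, the Gaussian log-likelihood contains the term −(N/2) ln(v), where v is the week-0 variance. Each tenfold fall in v adds 27 × 2.3026 = 62.2. The computed values for remission agree:

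- v = 0.1: 125.4
- v = 0.01: 187.6
- v = 10⁻⁴: 311.9
- v = 10⁻⁸: 560.6
- v = 10⁻¹²: 809.3

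There is no maximum. These are maximum-likelihood values with a separate mean for each arm and visit; REML changes the multiplier, not the divergence. AIC would favour any structure with its own week-0 variance, if the software reports that structure as converged.

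**4. The common-variance fallback.** This does run.

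- *Type I error.* Simulated with 4000 null trials, 23 per arm, complete data, SD 6, correlations 0.45 to 0.65 and mean scores 16, 14 and 13 (all assumed). The interaction test rejected at 0.062 for responder and 0.055 for remission, Monte Carlo SE 0.003. A plain week-21 t-test on the same data gave 0.054 and 0.048.
- *Diagnosis.* With two visits, complete data and a baseline of 0, each patient's change equals the week-21 value. The interaction is then the week-21 difference in proportions. In small simulated sets of 23 per arm its SE matched the ordinary pooled two-sample SE (for example 0.1317 against 0.1317).
- *Fitted values.* If time is linear, fitted probabilities can leave the 0 to 1 range, but only slightly in the one case examined. The pooled responder proportions in the 27-per-arm set were 0, 0.130 and 0.426. The slope is 0.426 / 2 = 0.213, the mean is 0.185, and the fitted week-0 value is 0.185 − 0.213 = −0.028.

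**The case against.** The strongest reply has four parts.

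**The fallback clause.** The plan foresees non-convergence, and a simple structure gives nearly correct error rates. This stands as a limit on the harm. It does not repair the rule: the clause changes only the covariance structure, keeps the Gaussian model and the constant week-0 row, and selects by a criterion that rewards the degenerate structures.

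**Loose shorthand.** Because the Secondary outcomes section places these measures at week 21, the authors may never have meant to include week-0 rows for them. That is plausible, but the linear mixed model is named explicitly for secondary measures and no other method is given. The two sections therefore still need reconciling. Nor is this detail left to an analysis plan that is not shown, since the article names a method and the method does not suit these outcomes.

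**The count.** A reader might add CGI improvement and infer that four of six outcomes are beyond the model. The documents do not support putting it in the same class. It is not a yes/no outcome and has no constant baseline; it simply has no week-0 value. A mixed model on weeks 10 and 21 would serve.

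**The consequences.** A reader might also infer that the model cannot be run, that its standard errors are wrong throughout, or that the trial's main result is at risk. None of these follows. A common-variance version runs with mild distortion, the two-visit diagnosis analysis reproduces the ordinary comparison, and the primary outcome is a continuous score that varies at baseline.

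**Conclusion.** The point holds for three of the six listed secondary outcomes: responder status, remission and absence of the baseline diagnosis. The stated unstructured fit is degenerate for them, and the fallback leaves a linear probability model whose covariance is settled after the data are seen. It should be fixed, but it does not threaten the primary analysis or the sample size.

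The structural result rests on the article's own definitions and entry criteria. For responder status it is exact. For remission and diagnosis it assumes that everyone analysed met the entry criteria; a patient randomised in error could make the week-0 variance slightly above zero, which would not help the model. The mild type I figures (0.062 and 0.055) rest on assumed means, SD, correlations and complete data, and show order of magnitude only.

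**What to change.** In the Statistical methods section, replace the blanket rule with one for each type of outcome, and align it with the week-21 timing in the Secondary outcomes section:

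- **SIGH-A and CGI severity:** keep the mixed model.
- **Responder, remission, absence of baseline diagnosis:** name a week-21 between-arm comparison suited to binary data. One acceptable choice is logistic regression adjusted for the allocation stratum and baseline GRID-HAMD, penalised if events are sparse, reported as a risk difference with 95 % CI. Other valid binary methods would do as well, provided one is named in advance.
- **Missing data:** derive response and remission from multiply imputed GRID-HAMD scores where these are missing (multiple imputation is already planned as a sensitivity analysis), and state a rule for a missing week-21 diagnosis.
- **CGI improvement (minor):** analyse post-baseline visits only, with no week-0 row.

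The cost is a few sentences and slightly more analysis work, with no new data. The Current study status section reports 44 participants enrolled against a target of 54 at submission, so at that point the change could still be made before the data were complete.
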